## Abstract

**Introduction:**

This research project addresses the lack of screening tools for the early detection of high-risk individuals for long-term care, through four individual studies.

Study 1 investigates the predictive ability of the ‘Kihon Check List’, study 2 the ‘Cognitive Function instrument’ and EuroQol-5 Dimension (EQ-5D) and study 3 the ‘Cognitive Function instrument’ and EQ-5D as well as the ‘Frail Kenshin’ health check-up, for incident long-term care certification over a follow-up period of up to 4 years. This is the first large prospective study to evaluate the predictive ability of these tools for the outcome measure long-term care certification. The last subsection of this project study four aims to explore a mixed methods intervention for delaying the need for long-term care. This section is purely exploratory, looking for clues for further studies.

**Methods and analysis:**

Baseline data have been collected through local government programs, as well as through postal self-reported questionnaires. The primary outcome variable for all studies is long-term care certification data. Statistical analysis will be carried out using Kaplan-Meier, Multiple Cox regression as well as logistic regression.

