### Outline of studies included in the project

The four studies are briefly explained below and summarised in table 1.

**Table 1 T1:** Summary of studies

	Study 1	Study 2	Study 3	Study 4
Target population for recruitment	General Population (80 000)	Citizens with Possible Cognitive Decline (4131)	‘Frail Check’ Participants (4800)	Brain health school programme participants (80)
Sample population	50 155	2385	2705	57
Baseline evaluation	KCL	CFI, EQ-5D, GDS	CFI, EQ-5D, General Frailty Measures	MMSE, EQ-5D CFI, GDS, etc
Primary outcome	LTC Need	LTC Need	LTC Need	MMSE
Secondary outcome	LTC Need Level	CFI, EQ-5D	LTC Need Level	EQ-5D, CFI, Five Cog, etc
Intervention	None	None	None	Intensive Cognitive Training
Study period	4–5 years	2 years	2 years	30 months

CFI, Cognitive Function Instrument; GDS, Geriatric Depression Scale; KCL, Kihon Check List; LTC, long-term care; MMSE, Mini Mental State Examination.

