#### Study 4: study on effect of multimodal dementia prevention programme in community-dwelling elderly

This is a parallel exploratory intervention study, to explore the effects of multimodal interventions for slowing the process of cognitive decline. The target group were approximately 80 citizens over 70 years old who participated in a dementia prevention education programme which was held monthly by Kobe city in 2016. Individuals who agreed to participate in this study are randomly divided into two groups. Both groups undergo an intensive training programme (education, cognitive training and exercise) once a week for a total of 10 weeks and are monitored every 6 months for up to 30 months after recruitment. During the follow-up period, the intervention group receives a booster training once every 3 months, whereas the control group does not. The endpoints include changes in Mini Mental State Examination, CFI, EQ-5D, Five Cog, Timed Up & Go test, Physical Activity Scale for the Elderly and Geriatric Depression Scale. In the ANOVA between the three groups, effect size was set at 0.25, α=0.05 and power=0.80, the necessary data number will be approximately 50 persons for each group. Since this is a long-term longitudinal study, the number of subjects is set at a higher 100 persons, which is about double the necessary number (for statistical significance) as a cautionary measure for drop outs and missing data. The longitudinal change of the evaluation results in each group is analysed using repeated ANOVA and mixed effects model. The amount of change in the evaluation result between groups is compared by multiple comparison tests: the paired t-test or Wilcoxon test.

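### Study 4: the abstract makes long-term care certification the primary outcome where Table 1 has MMSE, and the randomised groups differ only in the booster, not in the programme the study is named after

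*Protocol article*

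**What the plan says.** **Primary outcome.** The Abstract, under Methods and analysis, makes no exception for Study 4: "The primary outcome variable for all studies is long-term care certification data". The analysis methods it names are Kaplan-Meier, Cox and logistic regression. Table 1, in the outline of the studies, reads across Studies 1 to 4: "Primary outcome LTC Need LTC Need LTC Need MMSE". The Study 4 section lists seven endpoints (MMSE, CFI, EQ-5D, Five Cog, Timed Up & Go, a physical activity scale and a depression scale). LTC certification is not among them.

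**Aim.** The Abstract's Introduction says "study four aims to explore a mixed methods intervention for delaying the need for long-term care". The Study 4 section says the study is "to explore the effects of multimodal interventions for slowing the process of cognitive decline", and the end of Background and purpose agrees with that.

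**Intervention.** The Study 4 heading announces a "study on effect of multimodal dementia prevention programme in community-dwelling elderly", and Table 1 gives the intervention as "Intensive Cognitive Training". In the design text, participants are randomised into two groups and "Both groups undergo an intensive training programme", weekly for 10 weeks. During follow-up of up to 30 months, one group has booster training every 3 months and the other does not.

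**The concern.** Two things do not line up. First, the article gives Study 4 two different primary outcomes and two different aims, and all four statements are current text. Someone checking a later report of Study 4 against the Abstract would expect an LTC result; someone checking it against Table 1 would expect MMSE. Either could be cited as the outcome fixed in advance.

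Second, the heading and the Table 1 intervention cell suggest that the randomised comparison tests the multimodal programme. Because both groups receive that programme, a difference between them cannot be attributed to it. A booster result, or an improvement from before to after the shared course, could later be reported as a programme effect without the support of randomisation.

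This matters because Study 4 is the only intervention study in the project, and the Discussion (Meaning of study) looks forward to an early intervention model tied to LTC as the outcome.

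**Working it through.** The point rests on comparing statements, so they are set side by side.

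| Item | Abstract, heading or Table 1 | Design text for Study 4 | Consistent? |
|---|---|---|---|
| Primary outcome | Abstract: LTC certification, all studies. Table 1: MMSE for Study 4 | Seven scales listed, MMSE first; LTC certification not listed | Abstract conflicts with Table 1 |
| Aim | Abstract: delay the need for LTC | Slow cognitive decline (also in Background) | No |
| Analysis | Abstract: time-to-event and logistic methods | Repeated ANOVA and mixed model for changes in scores | Abstract's methods suit an LTC outcome, not Study 4's scores |
| Intervention | Heading: multimodal programme. Table 1: intensive cognitive training | Programme in both groups; booster in one | Label does not name what differs |

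**What randomisation identifies.** Let P be the effect of the 10-week programme and B the added effect of the booster after it.

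- Intervention group: P + B
- Control group: P
- Difference: (P + B) − P = B

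P cancels. Change within a group over the 10 weeks contains P, but also practice effects, regression to the mean and time, and the two groups described offer no comparison that separates them.

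**Does the sample-size sentence settle either question?** It gives effect size 0.25, α = 0.05, power 0.80 and about 50 per group, in an ANOVA of three groups. It names no endpoint, so it does not choose between MMSE and LTC. On the number of groups, take 0.25 as Cohen's f (an assumption) and use the noncentral F distribution with λ = N·f².

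- Three groups, one-way: 53 per group, N = 159, λ = 159 × 0.0625 = 9.94, power 0.805. At 50 per group, λ = 150 × 0.0625 = 9.375 and power is 0.780. The stated figure is reproduced only approximately.
- Two groups, one-way: 64 per group, N = 128, λ = 128 × 0.0625 = 8.0, power 0.801.
- Two groups, two repeated measures with correlation 0.5 (assumed), λ = N·f²·m/(1 + (m − 1)ρ): 49 per group, N = 98, λ = 98 × 0.0625 × 2/1.5 = 8.17.

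About 50 per group is thus close to a three-group one-way calculation and also to a two-group repeated-measures one. The figure does not show which design was meant, so the mention of three groups stays unexplained beside the two groups randomised.

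**The case against.** The best defence is that this is loose wording in a sub-study openly called exploratory. The Abstract says that Study 4 only looks for clues, and its small size is admitted twice. Delaying LTC can be read as the ultimate goal of the whole project. The Study 4 section states plainly that both groups train and that only one receives boosters, and the booster can be seen as part of a multimodal programme. All of that is fair, and it keeps the point at the level of a correction to the text. It does not remove it: an exploratory study still needs one primary outcome and an accurate account of its comparison, and the Abstract's sentence covers all studies without exception.

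Three stronger readings are tempting, and the document does not support them.

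- *A reader might infer that LTC data are not collected in Study 4.* The endpoint lists are open-ended, and certification is routine municipal data. Only its absence from the listed endpoints can be stated.
- *A reader might infer that any of the seven scales could be chosen as primary afterwards.* Table 1 names MMSE as primary and places EQ-5D, CFI, Five Cog and others as secondary. The conflict is between two candidates, so a multiplicity calculation over seven does not measure it. Nor is it a fault that the Study 4 section does not repeat the word primary or fix a visit; an analysis plan may supply the visit.
- *A reader might infer that every participant is trained and that no untrained comparison exists.* The sample-size sentence refers to three groups, and the Methods opening mentions a study 4a, neither explained. Table 1 gives 57 as the sample population without saying how many were randomised and trained. What is certain is that the two randomised groups described both receive the course.

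**Conclusion.** The point holds as a contradiction in the text with a consequence for interpretation. The Abstract's statement on the primary outcome is wrong for Study 4 if Table 1 is right, and the listed endpoints and score-based analysis side with Table 1. The Abstract's aim of delaying LTC need is matched by no listed Study 4 endpoint. As described, the randomised comparison estimates only the effect of adding boosters after a common programme; it gives no randomised estimate of the programme itself.

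No numerical bias is attached to this. An expected number of LTC events in Study 4 would depend on which risk stratum its participants resemble, and the prior Kobe 3-year incidences quoted in the Discussion run from 3.5% to 29.6%, too wide a span to be useful here. The conclusion assumes that the two-group description in the Study 4 section is the operative design. If a third, untrained group exists, the article would have to describe it, and say whether it was randomised, before any wider claim could be considered.

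**What to change.** 1. Abstract, Methods and analysis: limit the LTC primary outcome to Studies 1 to 3, and state change in MMSE as the primary outcome of Study 4, as in Table 1. Add the repeated-measures and mixed-model methods, or make clear that the methods named apply to Studies 1 to 3.
2. Abstract, Introduction: reword Study 4's aim as slowing cognitive decline. If LTC is to stay in view, list linked LTC certification as a descriptive secondary outcome of Study 4.
3. Study 4 section and Table 1: state the randomised question as booster versus no booster after a common programme, and make the intervention cell name what differs between the groups.
4. Label change from before to after the common programme as uncontrolled and descriptive.
5. Reconcile the three groups in the sample-size sentence with the two groups randomised: either describe the third group or correct the sentence and its calculation.

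Items 1 to 4 are changes of wording and need no new participants or visits. Listing LTC as a secondary outcome would require the link to municipal data for Study 4, if it is not already planned. Item 5 may mean redoing the sample-size calculation. The real cost is that Study 4 will claim less than it does now.

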**Conclusion:**

This project hopes to identify tools effective in predicting long-term care need. This will enable identification of citizens that are of higher risk for long-term care in the near future. This subset of high-risk individuals can in the future be addressed for extra support/intervention.

**Ethics and dissemination:**

All studies have been approved by respective institutional ethical committees and the WHO ethical committee ERC.0002899. In addition, all studies conform to the provisions of the Declaration of Helsinki and are conducted in accordance with Japan’s ‘Ethical Guidelines for Medical and Health Research Involving Human Subjects’. All findings will be disseminated at conferences and published in peer-reviewed journals.

**Trial registration number:**

UMIN000023283.

Strengths and limitations of this studyThis research project includes population based studies that allow for simple and reliable assessments of the risk for future long-term care need.This research project uses big data, which are collected by the local government (municipal office).The various baseline measures give a broad instrument to use for the prediction of long-term care needs concomitant with cognitive decline.The duration of follow-up of respective studies, which range from 2–4 years, is limited and further longer-term studies will be required.Study 4 has limitations, since it is a small sample and limited single-centre intervention study.

## Background and purpose

Due to high life expectancies and low birth rates, Japan has a rapidly ageing population. Since 2010, the proportion of population 65 years and older increased over 21%, making Japan a super-aged society.^1^ In 2019, this proportion reached 28% of the population.^2^ One of the major healthcare challenges is an increased need for long-term care (LTC). Dementia is one of the leading causes for care-requiring status, accounting for nearly 17% of individuals in LTC.^3^ Furthermore, the heart-breaking nature of the disease, accompanied with the significant impact on families and society, makes it a public health priority.^4^ Japan has the highest dementia prevalence (2.3% of the population) among Organisation for Economic Co-operation and Development (OECD) countries in 2017, and is projected to reach 3.8% by 2037.^5^

In spite of the urgent need to reduce the social burden, there are currently no therapeutic strategies to halt or slow the disease process.^6 7^ Lessons from prior studies recommend a focus on preclinical dementia and targeting of potential high-risk individuals who might benefit the most.^8^ In line with such recommendations, the focus of dementia research is shifting to earlier stages of cognitive decline, in the hope of mitigating or even reversing the pathophysiological processes.^9 10^ The achievements are still limited, in part due to the lack of efficient screening and evaluation methods for detecting higher risk individuals in society.

Under these circumstances, the Japanese Ministry of Health, Labour and Welfare (MHLW) issued a 5-year plan in 2013, for advancing measures against dementia, called ‘The Orange Plan’.^11^ In accordance with this plan, every municipality began to provide a variety of civil services in an attempt to tackle dementia, hoping to reduce the increasing social burden. For example, Kobe, the sixth largest city in Japan, initiated social participation programmes, aiming to prevent or mitigate cognitive decline, including the ‘Kihon Check List’ (KCL) programme, brain health school programme, and senior college programme. The effects of such services, however, have not been adequately evaluated due to the lack of appropriate evaluation metrics, and thus, improvements were hampered. Furthermore, LTC need data, is independently certified in the municipal office, with no link to dementia or other health promotion civil services.

The current project was designed to enable earlier identification of individuals at risk for dementia and consequently LTC. The first three studies use various cognition related questionnaires in an attempt to predict LTC need and identify individuals at higher risk. The last study is a small exploratory study which explores possible early interventions in these high-risk individuals to slow the progression of cognitive decline. This article introduces and outlines four individual studies included in this project.

## Methods

The current project comprises of four individual studies focusing on cognition-related parameters and LTC need certification in healthy community-dwelling citizens in Kobe city. Eligibility criteria of respective studies are independently defined, depending on the purpose of each study. Studies 1 and 4a were approved by the Ethics Committee in February 2017 and studies 2 and 3 in March 2017. All studies are currently ongoing.

### Evaluation and outcome measures

Questionnaires used in these studies are available in online supplemental files 1–5.

10.1136/bmjopen-2021-050948.supp1Supplementary data

10.1136/bmjopen-2021-050948.supp2Supplementary data

10.1136/bmjopen-2021-050948.supp3Supplementary data

10.1136/bmjopen-2021-050948.supp4Supplementary data

10.1136/bmjopen-2021-050948.supp5Supplementary data

#### Kihon Check List

KCL is a self-reported frailty questionnaire designed by the MHLW, to identify frail elderly individuals at risk for LTC. The questionnaire used can be found in online supplemental file 1. It consists of a 25-item self-reported questionnaire and has been widely delivered to citizens from local governments across the nation from 2006 to 2016. It covers several domains of instrumental activities for daily living (ADLs), including general independence, physical strength, nutritional status, oral function, housebound, cognitive function, depression risk and general health status. In particular, the KCL includes three cognitive function-related questions—Do your family or your friends point out your memory loss? Do you make a call by looking up phone numbers? Do you find yourself not knowing today’s date?

#### Cognitive Function Instrument

Cognitive Function Instrument (CFI) is a screening tool to detect early changes of ADL due to cognitive decline.^12^ It was developed by the Alzheimer’s disease Cooperative Study over the last decade. The questionnaire used can be found in online supplemental file 2. CFI consists of 14 questions that are related to functional ability changes as a result of cognitive impairments. It is brief and easily administered at home through post, telephone or transmitted electronically. The CFI score is calculated by summing 1 point for ‘Yes’, 0 point for ‘No’ and 0.5 for ‘Maybe’. Although the CFI questionnaire includes ‘self’ and ‘partner’ versions, this project uses the ‘self’ version, because the current surveillance set up did not allow for both versions.

#### EuroQol-5 Dimension

EuroQol-5 Dimension (EQ-5D) is a standardised measure of health status developed by the EuroQol Group in order to provide a simple, generic measure of health for clinical and economic appraisal. It is applicable to a wide range of health conditions and treatments. The questionnaire used can be found in online supplemental file 3. EQ-5D is designed for self-completion and is suited for use in postal surveys, in clinics, and in face-to-face interviews. It is officially available in 171 languages and the official Japanese language version has been selected for the purpose of this study. The EuroQol Group provides two version of the EQ-5D with 3 or 5 dimensions, the latter of which (EQ-5D-5-level (5L)) was adopted in this project. The EQ-5D-5L includes five categories with five questions in each category, summing up to 25 questions. Based on the pattern of answers, the health status of an individual is given a single index value, ranging from zero to one, death to perfect health.

#### Frail Kenshin

The ‘Frail Kenshin’ check-up is an elderly citizen health check-up programme by Kobe city, which is offered to citizens covered by the ‘Kokumin Kenko Hoken’ insurance (Kokumin Kenko Hoken is the National Health Insurance system in Japan, it includes all Japanese citizens and long-term residents). The questionnaires used along with this check-up can be found in online supplemental files 4 and 5. It has physically accessed components as well as self-assessed questions related to frailty. It evaluates, motor function, nutrition, oral function, forgetfulness, mental health, chewing ability, dental health, swallowing ability, grip strength, height (cm), weight (kg), body mass index and more.

#### LTC certification

Under the national LTC Insurance Act, certification of LTC need has been implemented since April 2000. The main beneficiaries are elderly individuals aged 65 or over. LTC need certification is routinely conducted by each municipal office on an application basis from citizens. LTC need status is categorised into eight levels (no need for support or care: 0, support level: 1 or 2, care level: 1–5). In the current project, certified care levels from 1 (partial assistance) to 5 (total assistance with disabled communication) were defined as to be in need of LTC.

So far, identification of individuals at higher risk of dementia has been hampered, largely because of the lack of convenient screening methods. Appropriate evaluation measures play a crucial role for the success of this project. For example, measures for baseline evaluation need to be easy to use, easy to answer, and quantitative. Also, measures for outcome evaluation need to be fitted for purpose, objective and must be readily observable in local governmental services. As measures to meet such requirements, KCL, CFI, EQ-5D and LTC certification have been chosen as some of the baseline and/or outcome evaluation tools. KCL has been proven to be a reliable indicator of frailty,^13^ and is considered advantageous for a population-based approach.^14^ EQ-5D is an established standard measure for health-related QOL, and is widely used around the world. In contrast, CFI is a relatively new measure, which could be used in large epidemiological and clinical studies with minimal in-person contact. In a previous study by Amariglio *et al*,^12^ the CFI score was gradually worse in individuals who developed dementia than in those that did not, over a period of 4 years. Although their finding does not directly demonstrate the utility of CFI for risk assessment of dementia, it suggests value to be tested in larger prospective studies. However, it should be noted that CFI is a measure for the change of ADL due to cognitive decline, and not a direct measure for cognitive function per se. Thus, the results to be obtained need to be interpreted with caution, yet it is a potentially useful tool for the risk stratification of LTC need in the community.

### Outline of studies included in the project

The four studies are briefly explained below and summarised in table 1.

**Table 1 T1:** Summary of studies

	Study 1	Study 2	Study 3	Study 4
Target population for recruitment	General Population (80 000)	Citizens with Possible Cognitive Decline (4131)	‘Frail Check’ Participants (4800)	Brain health school programme participants (80)
Sample population	50 155	2385	2705	57
Baseline evaluation	KCL	CFI, EQ-5D, GDS	CFI, EQ-5D, General Frailty Measures	MMSE, EQ-5D CFI, GDS, etc
Primary outcome	LTC Need	LTC Need	LTC Need	MMSE
Secondary outcome	LTC Need Level	CFI, EQ-5D	LTC Need Level	EQ-5D, CFI, Five Cog, etc
Intervention	None	None	None	Intensive Cognitive Training
Study period	4–5 years	2 years	2 years	30 months

CFI, Cognitive Function Instrument; GDS, Geriatric Depression Scale; KCL, Kihon Check List; LTC, long-term care; MMSE, Mini Mental State Examination.

